## Abstract

**Background:**

Necrotizing enterocolitis (NEC) is a leading cause of neonatal morbidity and mortality in premature infants. To date, no effective biomarkers exist to predict which premature infants will develop NEC, limiting targeted prevention strategies. Multiple observational studies have reported an association between the exposure to red blood cell (RBC) transfusion and/or anemia and the subsequent development of NEC; however, the underlying physiologic mechanisms of how these factors are independently associated with NEC remain unknown.

**Methods:**

In this paper, we outline our prospective, multicenter observational cohort study of infants with a birth weight ≤ 1250 g to investigate the associations between RBC transfusion, anemia, intestinal oxygenation and injury that lead to NEC. Our overarching hypothesis is that irradiation of RBC units followed by longer storage perturbs donor RBC metabolism and function, and these derangements are associated with paradoxical microvascular vasoconstriction and intestinal tissue hypoxia increasing the risk for injury and/or NEC in transfused premature infants with already impaired intestinal oxygenation due to significant anemia. To evaluate these associations, we are examining the relationship between prolonged irradiation storage time (pIST), RBC metabolomic profiles, and anemia on intestinal oxygenation non-invasively measured by near-infrared spectroscopy (NIRS), and the development of NEC in transfused premature infants.

**Discussion:**

Our study will address a critical scientific gap as to whether transfused RBC characteristics, such as irradiation and metabolism, impair intestinal function and/or microvascular circulation. Given the multifactorial etiology of NEC, preventative efforts will be more successful if clinicians understand the underlying pathophysiologic mechanisms and modifiable risk factors influencing the disease.

**Trial registration:**

Our study is registered in ClinicalTrials.gov Identifier: NCT02741648.

## Background

Necrotizing enterocolitis (NEC) is the most common gastrointestinal emergency among premature infants [1, 2], occurring in approximately 11% of those born < 29 weeks’ gestation [3]. Case-fatality rates are as high as 50% for extremely low birth weight (ELBW) infants (≤ 1000 g at birth) who develop NEC [4]. Survivors are at risk for substantial long-term complications including neurodevelopmental delay, nutritional deficit and failure to thrive [3, 5]. Costs associated with NEC in the United States are estimated at $1 billion annually [2]. Transfusion-related necrotizing enterocolitis (TR-NEC) refers to an observed phenomenon that specifically describes a premature infant who develops NEC within 48 h after receiving a red blood cell (RBC) transfusion. Several reports have identified RBC transfusions as a significant and independent risk factor for NEC [6–14]; however, others have not found an association [15–21], but rather an association with degree of anemia prior to NEC development, which has led to considerable controversy [18].

No current biomarkers reliably predict NEC, limiting efforts to prevent this disease. The range of symptoms are highly variable, from subtle signs such as feeding intolerance and abdominal distention, to complete cardiovascular collapse and shock. Because NEC can progress to extensive bowel necrosis within hours, therapies are often ineffective [22]. Multiple factors are related to NEC etiology including prematurity, enteral feeding, pro-inflammatory propensity of the immature intestine, and impaired mesenteric blood flow [23]. The majority of premature infants receive transfusions for anemia of prematurity, and RBC transfusions precede approximately 25–38% of NEC cases [7, 14, 24]. Transfusion of different storage aged RBCs to premature infants has not been shown to contribute to the risk of NEC [7, 24]. However, the chronological storage age of RBCs may not be an accurate gauge of donor RBC function and the storage lesion may be exacerbated by gamma irradiation [25], which is performed to prevent transfusion-associated graft-vs-host disease. Although the Age of Red Blood Cells in Premature Infants (ARIPI) trial investigated the effects of total storage duration of RBCs in preterm infants [26], the study did not investigate the effects of irradiation [27]. Currently, the “safe” duration of RBC storage following irradiation (post-irradiation storage time, pIST) is unclear. Given the multifactorial etiology of NEC, preventative efforts will be more successful if clinicians understand the underlying pathophysiologic mechanisms and modifiable risk factors influencing the disease.

Although premature infants weighting ≤1250 g at birth are frequently transfused for anemia of prematurity, optimal transfusion guidelines are ill-defined [28]. The Premature Infants in Need of Transfusion (PINT) trial [29] and the smaller Iowa trial [30] investigated the effects of transfusion practices on morbidity, although neither trial included NEC as the primary outcome. Because the PINT trial suggested lower hemoglobin thresholds decreased the number of RBC transfusions with no adverse effect on mortality, retinopathy of prematurity, or neurologic injury [29], many centers shifted to conservative transfusion practices. Concurrently, multiple published reports have described an association between RBC transfusion and NEC [6, 7, 10, 24, 31–33], although meta-analyses have shown conflciting findings regarding any association [11, 34]. The lack of adequately-powered randomized trials evaluating the effect of transfusion thresholds on NEC limit determination of whether increased tolerance of neonatal anemia by use of conservative transfusion thresholds may actually increase the risk of NEC.

A causal link between RBC transfusion and NEC has been proposed, but not proven. Our previous research described a matched case-control study of 184 very low birth weight (VLBW) infants weighing ≤1500 g with NEC, and found a higher risk of late-onset NEC (after 4 weeks of age) in transfused infants (OR 6.7; 95% CI: 1.5–31.2) [8]. An initial meta-analysis of observational studies also showed increased risk of NEC in VLBW transfused infants [11], although a more-recent meta-analysis found no association [34] with findings consistent from our recent multicenter, prospective cohort study [18]. Many of the studies included in the meta-analyses [34] were observational and limited in causal inference; no studies have provided data regarding the potential underlying pathophysiologic mechanisms. While these studies identified risk factors for NEC, including severity of anemia and a developmental window at which NEC occurs, few studies have focused on characteristics of the donor RBC transfusion, such as pIST and metabolic/functional abnormalities. Therefore, the critical scientific gap that remains to be addressed is whether transfused RBC characteristics, such as irradiation and metabolism, impair intestinal function and/or microvascular circulation. Our current investigation aims to prospectively evaluate the relationship between pIST, RBC metabolomic profiles, and anemia on mesenteric oxygenation, as measured by near-infrared spectroscopy (NIRS), and NEC.

### Candidate biological mechanisms of NEC

A number of potential mechanisms and clinical factors with biologic plausibility support a potential causal connection between RBC transfusion in response to anemia and NEC, despite the limitations described previously. Underlying this association is a common central component of insufficient oxygen delivery to intestinal tissue from a combination of decreased oxygen carrying capacity (anemia) and/or decreased blood flow (cardiac output, vascular tone). Oxygen consumption and extraction in intestinal tissue beds can be continuously and non-invasively monitored by near-infrared spectroscopy (NIRS) through measurement of oxygenated versus deoxygenated hemoglobin in venous (75%) and capillary (25%) blood [35].

#### Severity of Anemia and oxygen delivery to intestines

Severe anemia, leading to decreased oxygen delivery, may cause intestinal injury that predisposes an infant to NEC. Alkalay and colleagues [36] demonstrated that infants who appeared clinically “stable” with either significant anemia (hematocrit < 21%) or milder anemia (hematocrit 22–26%) had high cardiac output and restricted intestinal blood flow. Singh calculated that each percent decrease in nadir hematocrit led to a 10% increase in odds for NEC (OR 1.10; 95% CI: 1.02–1.18; *P* = 0.01) [10]. In our retrospective study, infants who developed NEC after transfusion had lower hematocrits 1 week prior than those without NEC [8]. We also found lower mesenteric oxygen saturation (MES-rSO_2_) measured by NIRS during and after transfusions in infants who developed NEC, and enteral feedings given during RBC transfusion worsened this effect [9]. Furthermore, a recent prospective study from our group found the rate of NEC was significantly increased among VLBW infants with severe anemia (≤ 8 g/dL) in a given week compared with those who did not have severe anemia (adjusted cause-specific hazard ratio, 5.99 [95% CI, 2.00–18.0]; *p* = .001) [18]. However, no study to date has prospectively compared longitudinal hemoglobin/hematocrit measures, MES-rSO_2_, and development of NEC in this population.

#### The RBC storage lesion, irradiation, nitric oxide (NO), and NEC

RBCs mediate local blood flow to preferentially perfuse the most hypoxic tissues, a process termed hypoxic vasodilation [36]. Nitric oxide (NO) released by RBCs is a potential mediator [37]. However, RBCs can also scavenge NO, a vasoconstrictive activity that may be enhanced in transfused RBCs with longer storage [38, 39]. Therefore, transfusion of stored RBCs (“storage-aged RBCs”, saRBCs) or pre-storage irradiated saRBCs (which worsens storage lesion) [40, 41] may disrupt vascular tone and blood flow. In animal studies, blood vessels of the immature intestine vasoconstrict when NO is depleted [42–45]. Thus, in a preterm infant with anemia, NEC could result from two mechanisms: transfusion of saRBCs (including those with extended pIST) interacting with immature intestinal endothelium, which together synergistically reduce blood flow, causing tissue hypoxia and, in some cases, NEC.

##### Aims

The aims of this prospective, observational study are to (Fig. 1): 1) Determine the associations between RBC storage after irradiation (pIST), metabolic alterations in stored/irradiated RBCs, and changes in mesenteric digestive tract regional saturation of oxygen (MES-rSO_2_) measured by NIRS; 2) Compare in vitro measures of RBC function, and metabolic changes, between RBC products transfused to infants who develop NEC compared to matched control infants who do not; and 3) Explore the clinical implications of severe anemia (hemoglobin ≤8 g/dL) during the vulnerable “NEC window period” of 29–34 weeks postmenstrual age in the responses of infants < 1250 g to RBC transfusion. Our overarching hypothesis is that irradiation of RBC units followed by longer storage perturbs RBC metabolism and function leading to paradoxical microvascular constriction, mesenteric tissue hypoxia, and increased risk for NEC in transfused premature infants with already impaired intestinal oxygenation secondary to significant anemia.

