##### Study design

We will prospectively investigate, using an established birth cohort design [18, 46], the associations between RBC transfusion (including characteristics of transfused RBCs), anemia, intestinal oxygenation, and NEC. We specifically aim to understand the relationship between pIST, donor RBC metabolomics profiles, and recipient anemia on MES-rSO_2_, as measured by NIRS, and the development of NEC (Fig. 1). Although many studies have characterized the association between NEC and transfusion, none have focused on improving our understanding of the underlying pathophysiology, particularly the intestinal oxygenation changes preceding NEC. Further, the safety and efficacy of various blood banking practices including the preparation of storage-aged RBCs (saRBCs) and repeat donor exposure in recipients remains unclear. The safe threshold of saRBC+/− pIST in infants is not known and longer-stored saRBCs, either before or after irradiation, may potentiate the RBC storage lesion. This study may provide new knowledge regarding the potential benefit or harm of various blood banking practices and may identify new potential mediators of NEC.

The study schema (Fig. 1) illustrates how we aim to characterize the association between metabolic changes in transfused RBCs relative to pIST, and adverse effects in the recipient through two approaches: in vivo NIRS trend monitoring of intestinal oxygenation, and in vitro RBC functional studies. The schema explains how variables will be compared to evaluate primary and secondary endpoints for each specific aim. Our primary endpoint is changes in MES-rSO_2_ trends in response to transfusion of saRBC+/− pIST as measured by NIRS (Aim 1). Secondary endpoints are 1) to determine the hazard ratio of NEC comparing infants transfused with saRBCs with and without pIST; (2) examination of metabolomics fingerprints of transfused RBC (in vitro) among infants with and without NEC (Aim 2); and 3) impact of severity of anemia over time during the NEC window (29–34 weeks postmenstrual age) on MES-rSO_2_ (Aim 3).

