## Methods

All RBC transfusions given to infants during hospitalization will be studied. All RBC transfused units are stored in citrate-phosphate-dextrose-adenine (CPDA-1) preservative solution. pIST and storage days will be recorded for each RBC transfusion. All infants will be monitored with NIRS prior to, during and up to 48 h following each transfusion. Consistent with epidemiologic reports of transfusion-related NEC and prior studies at the 3 centers, we anticipate approximately 20 (10%) infants will develop NEC while on study. For our 2:1 case-controlled metabolomic analysis, we will prospectively analyze 40 infants who do not develop NEC and compare to 20 infants with NEC. Within this sub-cohort, we will compare alterations in metabolic pathways from saRBC unit (in vitro) and infant blood sample (in vivo). We will then examine a third sub-cohort of 120 infants without NEC within the NEC “window” (29–34 postmenstrual weeks’). These infants will also be monitored weekly for 24–48 h with mesenteric NIRS to evaluate the relationship between anemic (hemoglobin < 8 g/dL) and non-anemic infants. Reports suggest that this specific population of infants are more likely to experience paradoxical reductions in MES-rSO_2_ substantially increasing the risk for NEC when transfusions are given [10, 36]. Analysis will also include assessment of hemoglobin as a continuous variable.

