## Discussion

There is an urgent need for a large, hypothesis-driven, prospective study to examine the effect of both RBC unit and recipient factors on the physiologic perturbations that cause NEC [11]. Given that 75–90% of low birth weight infants receive one or more RBC transfusions [52, 53], it is reasonable to predict that NEC may result from a combination of pre-existing anemia and reduced intestinal oxygenation exacerbated by metabolic/functional changes in transfused RBCs, due to irradiation and pIST. This investigation may allow us to identify new modifiable factors that can be used to test targeted prevention strategies and mitigate this devastating disease.

We propose to investigate intestinal oxygenation changes that precede the development of NEC. Our overarching hypothesis is that irradiation of RBC units followed by longer storage times perturbs donor RBC metabolism and function, and these derangements are associated with paradoxical microvascular vasoconstriction, intestinal tissue hypoxia and injury and/or NEC in transfused premature infants with already impaired intestinal oxygenation due to significant anemia. Specifically, our primary goal is to characterize the association between metabolic changes in transfused RBCs relative to pIST, and adverse effects in the recipient by in vivo NIRS trend monitoring of intestinal oxygenation, and in vitro RBC functional studies. Our primary endpoint is changes in MES-rSO_2_ trends in response to transfusion of saRBC+/-pIST as measured by NIRS. The secondary endpoints are to determine the hazard ratio of NEC for low birth weight infants transfused with saRBCs +/-pIST, examine metabolomic fingerprints of transfused RBC in vitro, and examine the impact of anemia severity on MES-rSO_2_ trends.

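### Aim 3 concerns the response to RBC transfusion in severe anemia, but its stated endpoint and weekly sub-cohort comparison are not tied to a transfusion

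*Protocol article*

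**What the plan says.** The protocol article describes Aim 3 in four places.

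- **Aims:** the implications of severe anemia during the 29–34 week PMA window "in the responses of infants < 1250 g to RBC transfusion". The outcome is a response to transfusion.
- **Study design:** the endpoint labelled Aim 3 is the "impact of severity of anemia over time during the NEC window" on MES-rSO2. No transfusion and no change score is named.
- **Discussion:** the matching secondary endpoint is to "examine the impact of anemia severity on MES-rSO_2_ trends", again without a transfusion.
- **Methods, opening paragraph:** "We will then examine a third sub-cohort of 120 infants without NEC within the NEC" window. It continues: "These infants will also be monitored weekly for 24–48 h with mesenteric NIRS to evaluate the relationship between anemic" and non-anemic infants. The reason given is that such infants are thought more prone to paradoxical falls in MES-rSO2 at transfusion.

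The same Methods paragraph also states: "All infants will be monitored with NIRS prior to, during and up to 48 h following each transfusion". Primary outcome sets a baseline of at least 30 minutes before transfusion. Statistical methods defines the change in mean area under the fitted curve (MAUC) from baseline to post-transfusion. It compares that change by pIST status, with a regression that admits other factors.

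**The concern.** A weekly recording made without reference to a transfusion gives a level of MES-rSO2. It has no before/after contrast and so contains no response. An analysis that follows Study design and Methods as written would relate hemoglobin to mesenteric saturation, which is a different quantity from the one Aim 3 names.

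The difference matters for interpretation. The article's own background explains that anemia lowers oxygen delivery to the intestine, so a lower level in anemic infants is expected whatever transfusion does. It would not show that severely anemic infants respond paradoxically to transfusion, which is the mechanism in the overarching hypothesis. With the aim pointing one way and the endpoint another, either quantity could be reported as the Aim 3 result once the data are known.

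**Working it through.** **1. Aim against endpoint and analysis**

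| Section | Outcome | Tied to a transfusion? |
|---|---|---|
| Aims, Aim 3 | Response to RBC transfusion, severe anemia, 29–34 weeks PMA | Yes |
| Study design, Aim 3 endpoint | MES-rSO2 by anemia severity over time | No |
| Discussion, anemia endpoint | MES-rSO2 trends by anemia severity | No |
| Methods, sub-cohort of 120 | Weekly 24–48 h recordings, anemic vs non-anemic | No |
| Methods, reason for the sub-cohort | Paradoxical falls at transfusion | Yes |
| Statistical methods | MAUC change, compared by pIST | Yes, but anemia is not named as the exposure |

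Study design and the Discussion both word the primary endpoint explicitly as a change in response to transfusion. The absence of those words from the anemia endpoint in both places is therefore a real difference in what is stated.

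**2. Are the response data planned?** Yes. Peri-transfusion NIRS covers all infants and every transfusion. The weekly sessions are an addition: "These infants will also be monitored weekly for 24–48 h with mesenteric NIRS". A baseline and a change measure are defined.

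**3. Sub-cohort size against monitored transfusions.** Inputs: 120 infants without NEC and about 20 NEC cases (Methods); 110 infants, fallback 72, transfused and NIRS-monitored (Sample size estimation).

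The smallest number of the 120 without a monitored response is 120 minus the monitored transfused infants without NEC, taking every such infant into the sub-cohort:

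- If no NEC case is among the monitored transfused infants: 120 − 110 = 10; fallback 120 − 72 = 48.
- If all 20 are: 120 − (110 − 20) = 30; fallback 120 − (72 − 20) = 68.

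All four are minimums. For illustration, assume that the 120 are a random draw from the 220 − 20 = 200 infants without NEC. With 110 monitored, the share with a monitored transfusion is 90/200 = 45% to 110/200 = 55%, so 120 × 0.45 = 54 to 120 × 0.55 = 66 infants would lack one. Restricting to transfusions inside 29–34 weeks PMA can only reduce the usable number further.

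**4. Power.** The article gives no power figure for Aim 3. Its Aim 1 figure reproduces. With 55 per group, difference 10, SD 18 and two-sided alpha 0.05 (assumed, as it is not stated):

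- SE = 18 × √(2/55) = 3.43.
- Power = Φ(10/3.43 − 1.96) = 0.83; the t-test gives 0.823. Table 1 gives 0.82.

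The same difference and SD can be applied to transfusion response in severely anemic versus other infants. The severely anemic share is not given, so 10% to 50% is assumed:

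| Monitored transfused infants | 10% | 20% | 30% | 50% |
|---|---|---|---|---|
| 110 | 0.41 | 0.64 | 0.75 | 0.82 |
| 72 | 0.28 | 0.45 | 0.57 | 0.64 |

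These count every monitored transfused infant once. Restriction to the window would lower the numbers.

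**The case against.** A reader might infer that Aim 3 as worded cannot be answered by this study. The document does not support that. NIRS is planned around every transfusion, the weekly sessions come on top, and the baseline, the change measure and a regression framework all exist. What falls short is the stated endpoint.

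Other counter-arguments have some force:

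- **The comparison may be in Fig. 1.** Study design says the schema explains how variables are compared for each aim, and the figure is not shown. Its caption, however, also describes the anemia part without a transfusion. Detail for an exploratory aim may properly sit in a fuller document, but the finding here is a conflict between stated sections.
- **The weekly endpoint has its own value.** The hypothesis presupposes intestinal oxygenation already impaired by anemia, and weekly levels bear on that premise directly. This stands, and it is why the weekly endpoint should be kept. Nothing in the article says that weekly levels will be used to conclude on transfusion response; that is a risk of the mismatch.
- **The 120 are never defined as transfused infants.** True. Exceeding 110 is a misfit only if the sub-cohort is meant to serve Aim 3 as worded.
- **The 110 are not all transfused infants.** Also true: the figure counts infants transfused and monitored. The Discussion cites transfusion in 75–90% of low birth weight infants, which for 220 would be 165 to 198. If monitored transfusions approached that number, the minimum shortfall would vanish. The shortfall rests on the plan's own assumption.

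**Conclusion.** The mismatch holds. Aims words Aim 3 as a response to transfusion; the endpoint in Study design and the Discussion, and the weekly comparison in Methods, are not tied to a transfusion. The only transfusion-response analysis described is by pIST. The stated endpoint therefore does not answer the aim, although the data needed to do so are planned.

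On the plan's own figures, at least 10 of the 120 sub-cohort infants (fallback at least 48) cannot contribute a monitored transfusion response. A reader might take 10 to 30, or 48 to 68, as the range of infants affected. Those figures are minimums, because they assume that every eligible monitored infant is among the 120, and the article does not say how the 120 are chosen. The 120 should not be read as the sample size for Aim 3 as worded.

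The aim is exploratory and its endpoint secondary, so the primary analysis is unaffected. The point should still be corrected, because correction is cheap and fixes beforehand which quantity Aim 3 reports.

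**What to change.** Reconcile Aims, Study design, Methods and the Discussion in one of two ways.

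1. **Keep the aim (preferred).** Add, as the Aim 3 transfusion-response endpoint, the baseline to post-transfusion MAUC change for transfusions given at 29–34 weeks PMA. Relate it to the last pre-transfusion hemoglobin, both as severe anemia versus not and as a continuous variable. State its own sample: infants with at least one monitored transfusion in the window. Keep weekly MES-rSO2 by hemoglobin as a separate named endpoint, and say that it will not be used to conclude on transfusion response.
2. **Keep the endpoint.** Reword Aim 3 to the relation between anemia severity and MES-rSO2 in the window, and drop the claim about transfusion response.

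The first option needs revised wording and one further analysis of recordings already planned. Its downside is a smaller stated sample and limited power, which should be acknowledged alongside the exploratory status of the aim. The second needs wording only, but gives up a direct test of whether anemia modifies the response to transfusion.
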